## Abstract

**Background:**

Health service programmes frequently encounter challenges with patient adherence to care. A promising, low-risk approach to address this issue is providing patients with targeted information about the importance of adherence. In the Vision Impact Project (VIP), an eye health screening programme in Kenya, the adherence rate to attending triage clinics after referral is around 50%. To improve this rate, this trial will test the effectiveness of delivering relevant information to patients at the point of referral along with reminder messages.

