**Methods:**

A pragmatic, Bayesian adaptive trial will be conducted within the VIP programme to assess the effectiveness of providing enhanced information compared to standard care. Weekly interim analyses will monitor adherence rates to referral appointments following positive vision impairment screenings. Participants will be randomized equally into intervention and control groups. The trial will stop if interim findings indicate either efficacy of one arm over the other, or futility that the two arms are performing equally.

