## Introduction

### Background and rationale

Health service programmes often face challenges in improving patient adherence, particularly in screening initiatives designed to identify and connect patients with care. This issue is evident in vision impairment (VI) screening, where timely access to care is crucial for enhancing quality of life and preventing avoidable complications such as blindness. Peek Vision (
https://peekvision.org), a social enterprise, aims to address the global burden of VI by providing eye screening and patient management tools that facilitate referrals to local healthcare systems. To date, Peek Vision has screened over eight million people worldwide, identifying about 1.6 million in need of eye care. Despite the efforts, internal data shows that adherence rates are around 50%, revealing a gap in connecting patients to care.

In the Vision Impairment Project (VIP) based in Kenya, which employs Peek Vision’s screening platform, similar trends have been observed. Young adults aged 18–44 show particularly low adherence rates around 30%, highlighting the need for targeted interventions for this group. Interviews and surveys with these young adults have identified key barriers and potential solutions to improve adherence
^
1
^. One promising strategy is to provide information about the importance of care to increase awareness and encourage health-seeking behaviour.

These service modifications are low-risk and expected to yield modest improvements on attendance. Traditional, fixed-duration trials to test such incremental changes could be resource-intensive and time-consuming. As an alternative, we will conduct a pragmatic adaptive trial within the VIP programme, leveraging accumulating data and early stopping rules. The trial will assess whether providing additional information at the point of referral and via SMS reminders can enhance adherence and increase the proportion of people attending triage clinics. The trial setting, eligibility criteria, intervention definitions, and outcomes measurements have been described in detail in the study protocol
^
2
^. This paper expands on the protocol by providing a detailed statistical analysis plan.

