### Outcomes

The programme will enrol all eligible adult participants. But the primary outcome will focus on the proportion of attendance in adults aged 18–44 years, who were identified in the formative research as the group less likely to attend appointments. Successful outcome will be defined as attending the scheduled appointment or within 14 days of the appointment date. A secondary outcome will measure overall attendance rates within 14 days of the appointment among all enrolled adults.

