### Interim analysis

Once the trial begins, interim analyses will be conducted every 7 days, with an average of about 300 adults aged 18–44 enrolled each cycle. The first interim analysis will take place after allowing a 14-day window for participants enrolled during the initial 7 days of the trial to attend their appointment on the scheduled date or within 14 days thereafter.

Bayesian methods will be used to analyse attendance in each arm. At each interim analysis, the proportion of attendees in each arm will be described using a binomial distribution of the outcome probability. This data will be combined with prespecified prior distributions through 10,000 Monte Carlo simulations to generate posterior distributions of the outcome proportions and the effect difference between the arms. These posterior distributions will be compared to predefined stopping rules to determine whether the trial should continue or stop. The decision to stop the trial will be solely based on the primary outcome, focusing on young adults aged 18–44.

We will use a uniform prior for the outcome probability of the control arm, specified as
*logit(p) ~ norm(0, 0.3)*, reflecting variability between 0 and 1
^
3
^. We will also use a neutral prior for the effect difference between the two arms, with an odds ratio of 1.0 and a 95% credible interval (95% CI) ranging from 1/30 to 30. This neutral prior allows for detection of a wide range of effect differences and ensures that the posterior distribution is primarily driven by trial data rather than specified prior beliefs
^
4
^, enhancing the generalizability of the results across various settings.

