### Final analysis

When one of the two stopping rules is met, the trial will terminate and proceed to the final analysis stage. The maximum duration of the trial is set at 1 year, with an estimated enrolment of 15,000 participants aged 18–44 years. If neither stopping rule is triggered within this timeframe, the trial will declare that the arms are equally effective, and the intervention will not be adopted. Upon completion of the trial, all accrued data will be analysed on an intention-to-treat basis.

**
*Baseline characteristics*.** Age and sex of the participants will be described according to allocation. Frequency and percentages will be reported for sex, while age will be summarized using mean and standard deviation. Data will be assessed for normality and checked for the presence of outliers.

**
*Primary and secondary outcomes*.** The primary outcome is attendance at the triage clinic
*among young adults between ages of 18 and 44*, and the stopping rules are based only on the analysis of this group. The secondary outcome is the proportion of attendance in
*all ages*. The final analysis will report the posterior probability of each arm being superior to another, and the posterior probability of the two arms having a negligible difference of 1% or less. Additionally, the posterior distributions of the outcome proportions in each arm will be described by mean and 95% CI. The posterior distribution of the effect difference between the arms will also be reported with mean and 95% CI (
Table 1).

**Table 1. T1:** Reporting final analysis results.

	Probability of being superior	Probability of having a negligible difference	Mean success probability	Mean effect difference (95% CI)
18–44 years (primary outcome)				
Intervention arm				
Control arm				
44+ years				
Intervention arm				
Control arm				
All adults (secondary outcome)				
Intervention arm				
Control arm				

Posterior probabilities of being superior and having negligible difference of <1% will be reported for each age group. In each arm, the mean success probability and its 95% credible interval will be reported based on the posterior distribution of probabilities of success.

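### The all-adult secondary difference reads as a pooled comparison; averaging the two planned age-group differences would make it somewhat more precise at little cost (optional)

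*SAP article*

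**What the plan says.** The secondary outcome is set out under Outcomes: "A secondary outcome will measure overall attendance rates within 14 days of the appointment among all enrolled adults". The abstract gives the allocation: "Participants will be randomized equally into intervention and control groups".

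The only outcome model in the document is under Interim analysis, where "the proportion of attendees in each arm will be described using a binomial distribution of the outcome probability". Final analysis names no other model and no stratum or covariate term. It does plan results by age: Table 1 has rows for 18–44 years, 44+ years and all adults, and its note says "Posterior probabilities of being superior and having negligible difference of <1% will be reported for each age group". The SAP does not say whether the all-adult row is pooled over age or built from the two age rows.

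At baseline, "Age and sex of the participants will be described according to allocation", and "Frequency and percentages will be reported for sex, while age will be summarized using mean and standard deviation".

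Two attendance rates are given. Background and rationale says "Young adults aged 18–44 show particularly low adherence rates around 30" per cent. The abstract says of the whole programme that "the adherence rate to attending triage clinics after referral is around 50" per cent.

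**The concern.** If 18–44s attend at about 30% and the programme as a whole at about 50%, older participants must attend considerably more often. A pooled proportion per arm leaves that between-age-group variation in the error of the arm comparison. The credible interval for the all-adult difference is then wider than the collected data require.

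This has some bearing here because Table 1 reports, for all adults, the probability that the difference is below 1%, and that probability depends directly on the width of the posterior. Recruitment also stops on the 18–44 results alone. The all-adult comparison must take whatever sample that leaves, so the choice of estimator is one of the few remaining ways to sharpen it.

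**Working it through.** The SAP gives no sample size, power or interval width for the all-adult comparison, so there is no stated figure to reproduce.

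**Inputs from the SAP**
- Attendance at 18–44: pY = 0.30 (Background and rationale).
- Attendance overall: p = 0.50 (abstract, Background).
- Equal allocation (abstract, Methods).
- 3,800 participants, the median sample size under a 1% effect (Stopping rules), used only to scale the interval and read as participants aged 18–44.

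**Assumption.** The share s of enrolled adults aged 18–44 is not stated. It is varied from 30% to 50%.

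**Formulas** (large samples, no treatment effect, influence of the priors ignored; N = all enrolled adults)
- Older-group attendance: pO = (0.50 − 0.30s)/(1 − s)
- Pooled difference: variance = 4p(1 − p)/N
- Age-weighted difference: variance = 4[s·pY(1 − pY) + (1 − s)·pO(1 − pO)]/N
- Proportion of variance removed: R = s(1 − s)(pO − pY)²/[p(1 − p)]
- Reduction in standard error: 1 − √(1 − R)

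**Example, s = 0.5.** pO = (0.50 − 0.15)/0.5 = 0.70. R = 0.25 × 0.40²/0.25 = 0.160. The standard error falls by 1 − √0.84 = 8.3%.

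| Share 18–44 | pO | Variance removed | Standard error smaller by |
|---|---|---|---|
| 30% | 0.586 | 6.9% | 3.5% |
| 40% | 0.633 | 10.7% | 5.5% |
| 50% | 0.700 | 16.0% | 8.3% |

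**Simulation check.** In 40,000 simulated trials with no effect, the variance removed was 7.0% at s = 0.3 and 16.1% at s = 0.5. Both estimators were unbiased.

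**On the scale of the result.** With 3,800 participants aged 18–44, N = 3,800/s and the pooled 95% half-width is 1.96/√N.
- s = 0.3: N = 12,667. The half-width goes from 1.74 to 1.68 percentage points.
- s = 0.5: N = 7,600. The half-width goes from 2.25 to 2.06 percentage points.

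**Sensitivity to the rounded 50%.** With an overall rate of 45%, the variance removed is 3.9% at s = 0.3 and 9.1% at s = 0.5. With 55%, it is 10.8% and 25.3%.

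**Sex.** The SAP gives no attendance rate by sex. Assuming an even split, 50% attendance and a gap of 5 or 10 points, R equals the squared gap: 0.25% or 1.0%.

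**The case against.** The strongest reply is that nothing here is wrong. An unadjusted arm comparison is valid under randomisation, and its interval already allows for chance age imbalance. The outcome is secondary: stopping and adoption rest on ages 18–44 only. The article is condensed, the binomial description is written for the interim analyses, and the all-adult row might already be meant as a combination of the two age rows. The 18–44 share is unknown, and the 50% is rounded and not stated to refer to adults only. The gain in interval width is modest, and no conclusion is shown to change.

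Most of this stands, and it limits the point to an optional improvement. It does not remove it. Pooling is the natural reading of the only model given, and across the shares and rates examined the gain is positive and almost free.

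A reader might infer more than the document supports:
- **That age is used only to describe the arms.** It is not. Age defines the primary and stopping population and structures Table 1.
- **That chance age imbalance biases the pooled estimate.** It does not. That imbalance is the same variance component that stratification removes, so it should not be counted as a second cost.
- **That sex should be adjusted for, or an adjusted primary estimate added.** No figure in the SAP supports a gain from sex, and none allows a gain within 18–44 to be calculated. Both would add modelling choices and priors that the plan does not specify.

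**Conclusion.** The point holds as an optional efficiency gain. As written, the all-adult difference makes no use of age group beyond separate reporting rows, although the plan's own rates make age group prognostic. For an assumed 18–44 share of 30% to 50%, averaging over the two age groups would remove about 7% to 16% of the variance. That is a standard error about 3.5% to 8.3% smaller, or at most about 0.2 percentage points of half-width in the worked example.

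The size rests on three assumptions: the unstated share, an overall rate close to 50% among enrolled adults, and priors that carry little weight. Allowing the overall rate to lie between 45% and 55% widens the variance range to about 4% to 25%. The result does not suggest that the planned analysis is invalid, and it leaves the primary result and the stopping rules untouched. Nor does it address the overestimation after early stopping that the SAP's Discussion concedes.

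**What to change.** Add one sentence to Final analysis, under primary and secondary outcomes. It should say that the all-adult posterior difference is the average of the 18–44 and older-group posterior differences, weighted by each age group's total enrolment over both arms. Its credible interval and the all-adult superiority and negligible-difference probabilities should come from the same weighted draws. The two groups must not overlap for this, so the older row should exclude age 44, which the 44+ label in Table 1 leaves open.

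Leave the primary analysis and the weekly stopping rule unchanged.

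The cost is that sentence and a few lines of R, because both age-group posteriors are already planned and age is already recorded. The SAP says that it was finalised before the trial began, and Study status reports data collection complete. If the sentence is added after the original plan, it should be labelled as such.

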### Statistical software

All analyses will be conducted in R using the “rjags” package, which interfaces to JAGS library for Bayesian data analysis. Interim analysis will be automated within the Peek Vision’s data collection and analysis software, Peek Capture, which utilizes prewritten R scripts. Alerts will be issued by Peek Capture when a stopping rule is met. A statistician from the London School of Hygiene and Tropical Medicine will also perform weekly manual audits to verify the algorithm functions as intended.

## Discussion

This article presents the statistical analysis plan for our published trial protocol, which aims to evaluate whether providing information about the importance of care improves patient adherence. This statistical analysis plan was refined and finalized before the trial commenced.

This study is classified a negligible risk trial, focusing on evaluating the effect of low-risk service modifications within a health service programme. We have designed an adaptive trial to facilitate early decision-making, enabling prompt adoption of an intervention that may yield a marginal improvement in outcomes. Simulations have demonstrated that our study design is sufficiently powered to detect an intervention effect as small as 1% with a modest sample size, suitable for our programme setting. Nonetheless, our study design permits a type I error rate that is higher than typically acceptable in many clinical trials (36.3%) in scenarios where there is no intervention effect. This was deemed acceptable both by the programme and the ethics board due to the negligible risk of adverse events. We note that the magnitude of the relative effect observed should be interpreted with caution, as the early stopping rule for efficacy may potentially lead to overestimation of this measure.

Fixed-duration trials can be costly, especially when evaluating interventions with potentially small effects. To improve adherence, health service programmes often resort to before-and-after studies. Through this trial, we aim to demonstrate the value of this pragmatic adaptive trial design for evaluating low-risk service modifications, and to encourage research bodies to consider this approach for improve access and adherence in health service programmes.

## Study status

At the time of protocol submission, eligible participants have been recruited and had completed data collection.

## Ethics approval and consent to participate

The study received ethics approval from the Kenya Medical Research Institute (KEMRI) scientific and ethics review unit, and from the London School of Hygiene & Tropical Medicine research ethics committee on February 6, 2024 (reference no. 29549).

This was a pragmatic trial being implemented within an ongoing screening programme. The Institutional Review Board (IRB) approved the use of oral consent, considering the intervention to be low-risk and aiming to minimise disruption to the ongoing screening programme. Screeners obtained consent during the screening process and documented it electronically using a tick box.

## List of abbreviations

CI        Credible Interval

SMS    Short Message Service

VIP     Vision Impact Project

## Data Availability

No data are associated with this article. Open Science Framework: SPIRIT checklist for <Enhanced patient counselling and SMS reminder messages to improve access to community-based eye care services in Meru, Kenya: statistical analysis plan for a Bayesian adaptive trial>
https://doi.org/10.17605/OSF.IO/T3YMF
^
7
^. Data are available under the terms of the Creative Commons Attribution 4.0 International license (CC-BY 4.0).
